## Abstract

Psychotherapy and antidepressant medication are considered first-line treatment options for major depressive disorder (MDD). However, a high proportion of patients do not respond to initial treatment, underlining the need for alternative treatment methods. Repetitive transcranial magnetic stimulation (rTMS) has been established in the treatment of MDD, but the available evidence is limited to forms of MDD with varying degrees of treatment resistance. Randomized-controlled trials (RCT) investigating first-line treatment with rTMS in comparison with first-line antidepressant medication are warranted to further position rTMS within current treatment algorithms for MDD. In this two-stage, therapy response-adapted, randomized multi-center phase 2 rater blinded trial, 106 medication-naïve patients suffering from MDD will be enrolled. In Stage I, participants receive one of the two treatment options for four weeks: either daily bilateral theta burst stimulation (TBS), a patterned and time-saving form of rTMS, or antidepressant medication with selective serotonin reuptake inhibitors (SSRI). The allocation to Stage II occurs therapy response-adapted. Therefore, patients either receive maintenance treatment or will be switched to the respective other treatment arm. Primary outcome is the comparison between the two study arms with regard to therapy response measured by the Montgomery-Asberg Depression Rating Scale (MADRS) after 4 weeks at the end of Stage I. The aim of the study is to provide reliable first evidence and effect size measures of rTMS as first-line treatment compared to SSRI treatment. Positive results will help to implement rTMS in early stages of MDD. Trial registration: ClinicalTrials.gov ID: NCT06545474, August 15, 2024.

## Background

Major depression (MDD), a mental illness with rising prevalence [1], severely impairs quality of life, autonomy, social integration and life expectancy [2]. Psychotherapy and medication are effective treatments of MDD. Nevertheless, a large proportion of patients do not respond sufficiently to the initial treatment [3] and approximately 60% will experience a recurrent or chronic course of illness under available treatment options [4]. Psychotherapy and antidepressant medication are considered first-line treatment opportunities in MDD. The often-insufficient response to antidepressants combined with limited psychotherapeutic treatment resources lead to undertreatment for many MDD patients. Non-pharmacological treatment options such as non-invasive brain stimulation techniques might provide the opportunity to better treat MDD. In particular, repetitive transcranial magnetic stimulation (rTMS) has been established as an effective treatment for MDD [5]. Although rTMS is safe, has few side effects and shows good efficacy [5–7], its use is still limited to forms of MDD, which respond inadequately to antidepressant treatment. In these patients, rTMS is superior to pharmacological treatment strategies such as switching or augmentation even in treatment resistant depression (TRD) [8, 9]. Evidence for the benefit of rTMS in early phases of the disease compared to a first pharmacological treatment is still lacking and therefore limits the use of this well-tolerated treatment option in this large and often underserved patient group [10]. With theta burst stimulation (TBS), a significantly shorter and more cost-efficient variant of rTMS is available. Based on recent evidence for non-inferiority [6, 11, 12], TBS has largely replaced conventional 10 Hz rTMS as the standard rTMS protocol in the treatment of MDD. As for TBS however, available evidence refers almost exclusively to MDD forms with variant degrees of treatment resistance. According to the current approvals and guideline recommendations, rTMS is predominantly considered after several unsuccessful treatment attempts.

However, based on its efficacy, favourable side-effect-profile, and high patients‘ acceptance, its use as first-line treatment of MDD seems obvious and promising [13]. For this purpose, studies investigating rTMS in early phases of depression, and particularly compared to other first-line treatments such as selective serotonin reuptake inhibitors (SSRI) medication and psychotherapy, are needed.

To our knowledge, a comparison of the efficacy of TBS and antidepressant medication in medication-naïve MDD patients does not exist. The few available studies are limited to rTMS as add-on treatment to ongoing antidepressant medication [14–16]. The recommendation of rTMS as a first-line treatment requires a head to head comparison to antidepressant medication. Therefore, we investigate rTMS as first-line treatment in an early phase of MDD by focusing on patients who have not received adequate antidepressant treatment before. Since SSRIs are by far the most commonly prescribed antidepressants in primary care, and escitalopram is one of the most widely used and well tolerated substances in this group [17], this SSRI will be used as comparator. Regarding the rTMS treatment protocol, we will follow most recent evidence and our own line of research [18–20] by augmenting left-sided intermittent TBS (iTBS) [20] with right-sided continuous TBS (cTBS) [20].

Insufficient treatment response is a common challenge in early phases of MDD [21]. For this, clinical guidelines recommend to check treatment success of antidepressant therapy after 3–4 weeks and, in cases of insufficient response, to adapt the treatment strategy accordingly. If rTMS is meant to be considered as a feasible first-line intervention in MDD, the question of the optimal sequence of interventions arises. It is also interesting to examine the extent to which patients’ preferences, beliefs, and expectations of treatment efficacy influence its success [22].

With this study, we aim to fill this knowledge gap accordingly. *First*, we want to provide reliable evidence and effect size measures of TBS compared to SSRI as an early intervention for MDD in medication-naïve patients. *Second*, we aim to obtain initial data about the influence of intervention order on the effectiveness of treatment and feasibility of the two-stage response-adapted treatment approach. *Third*, we will include patients’ real-world treatment preferences and shared-decision making elements in the course of the experimental therapy.

The results of this randomized comparison of rTMS as first-line treatment and SSRI will allow for the data-informed design of a full-size clinical trial with the potential to substantially change MDD treatment by expanding the indication for rTMS to early phases of MDD, re-evaluating the positioning of rTMS in the course of therapy and documenting the feasibility and efficacy of participatory decision-making. An expansion of therapeutic options, particularly in early phases of the disorder, is highly desirable for preventing treatment resistance and reducing chronic courses. Not least, an extended range of therapeutic options can increase treatment satisfaction and success by integrating patient’s preferences in individualized treatment planning.

## Design and methods

We will conduct a two-stage therapy response-adapted, rater-blinded, randomized (1:1 ratio) and controlled study (Fig. 1). Each stage will encompass a 4-week treatment. The follow-up phase covers a period of three months.

### Patient allocation to Stage I and Stage II and treatment modalities

For each patient the trial starts with obtaining written informed consent and checking the inclusion and exclusion criteria. In case of eligibility, randomization will determine whether a participant will receive one of two treatment approaches consistent with guideline-based clinical practice in ***Stage I*** (4 weeks) either 20 sessions of bilateral TBS (each weekday) or SSRI treatment (daily intake), respectively.

In ***Stage II*** (4 weeks), the allocation to the following treatment phase relies on the response to the treatment of Stage I. The decision will be made within the framework of a shared decision-making process. There are three different scenarios depending on the development of the Montgomery-Asberg Depression Rating Scale (MADRS) score after Stage I:

First, in the case of ***remission*** achieved after Stage I (remission is defined as MADRS score ≤ 10 points), patients will receive maintenance therapy i.e. maintaining the medication or continuing TBS in the sense of a TBS maintenance therapy (no TBS in week 1, 5 TBS sessions in week 2, no TBS in week 3, 5 TBS sessions in week 4 of Stage II). In this case, a shared decision-making process regarding further treatment is obsolete, as patients meet no longer the criteria for MDD.

Second, in case of ***non-response*** (MADRS score increase or reduction by < 50%), treatment condition will switch to the respective other arm. Continuation of ineffective treatment would be inconsistent with guideline-based clinical practice.

Third, in case of ***treatment response*** (MADRS score reduction by ≥ 50% compared to baseline), but not meeting remission criteria, maintenance treatment will be generally recommended. However, the patient’s individual preference will be considered and discussed. We will prepare a standardized and comprehensive patient information leaflet comprising comprehensible and detailed information regarding the mechanisms and (dis)advantages of the two treatment alternatives. Patients will thus be provided with information material that empowers them to make an informed decision on the individually preferred treatment condition in Stage II (maintenance or switch). We will document the patients’ individual reasons for their treatment preferences.

### Interventions

#### Bilateral TBS

In Stage I, bilateral TBS consists of 20 sessions administered daily from Monday to Friday over a period of 4 weeks. The target regions are the left and right dorsolateral prefrontal cortex (dlPFC), EEG position F3 and F4 respectively. Previous studies have shown a significant clinical improvement in depressive symptoms after a treatment duration of 4–6 weeks [23–25].

On the left hemisphere, iTBS is applied, which has a stimulating effect on the target region similar to 10 Hz rTMS [18, 19, 24]. On the right dlPFC, cTBS is applied, which has an inhibitory effect similar to 1 Hz rTMS [18, 19, 26]. Before and after each stimulation, a safety check is performed, including visual inspection of the target region as well as assessing and documenting the occurrence of (serious) adverse events.

### Stimulation localization, stimulation protocol, and technical devices

Based on the standard TBS protocols [27–29], each stimulation session consists of 600 biphasic stimuli applied in bursts of 3 pulses at 50 Hz, with an interstimulus interval of 200 ms. iTBS is administered 20 times for 2 s to the left dlPFC, with an intertrain interval of 8 s and cTBS continuously for 40 s to the right dlPFC in alternating order. A standard figure-8 coil will be used.

To individualize stimulation intensity, each patient’s resting motor threshold (RMT) is determined before the start of the first treatment session. RMT is defined as the minimum stimulus intensity that produces a minimal, visible motor response (in at least 5 of 10 trials) at rest. Stimulation intensity is set to 80% of the RMT for both iTBS and cTBS. The localization of the TBS target regions is based on the 10/20 EEG system. The left dlPFC corresponds to F3 and the right dlPFC to F4 [6, 30–32].

### Standard of care treatment with SSRI

SSRI are considered as a first-line treatment of at least moderate MDD [33]. Escitalopram (10 mg / day) will be administered as standard medication. In justified individual cases and according to the decision of the study physician, the prescription of a higher dose or another SSRI is possible. Before starting medication, a comprehensive physical examination, an electrocardiogram (ECG), and routine blood tests are performed to identify any potential contraindications that would exclude participants from the study. Each woman of childbearing age will carry out a pregnancy test. During treatment, participants are instructed to contact the study physician in cases of experiencing any adverse events (AEs). Adverse events/severe adverse events (AE/SAEs) are recorded on a daily basis on the designated documentation form.

### Study population

The study population comprises patients with at least moderately severe MDD. This can be either the first or a recurrent episode, but participants have to be medication-naïve according to the Antidepressant Treatment History File (ATHF) [34] for the whole history of MDD.

#### Inclusion criteria

Male, female, or diverse sex; age between 18 and 65 years; moderate to severe MDD according to the diagnostic criteria of DSM-5; MADRS Score ≥ 20 points; the duration of the episode must be at least 2 weeks and not exceed a period of 2 years; no previous antidepressant treatment according to the ATHF; indication for antidepressant medication; capability to give informed consent.

#### Exclusion criteria

Acute suicidal ideation (MADRS item 10 score > 4); presence of psychotic symptoms; antiepileptic drugs or benzodiazepines in a dosage equivalent to > 1 mg Lorazepam/d; comorbid axis I disorder (except anxiety disorders); presence of severe, clinically relevant, and predominant comorbid personality disorder; treatment resistance defined as the failure of at least one adequate antidepressant treatment attempt in the current or previous depressive episode; neurological pre-existing conditions such as severe traumatic brain injury, neoplasms, brain surgery, stroke within the last 3 months, neurodegenerative diseases: epilepsy or history of epileptic seizures; cardiac pacemaker (not compatible with MRI); intracranial metallic implants; previous rTMS treatment; deep brain stimulation; other severe somatic diseases; pregnancy; contraindications for the use of escitalopram.

### Ethics, consent and registration

Our study will be conducted in accordance with the principles of the Declaration of Helsinki and comply with the guidelines of Good Clinical Practice of the International Conference on Harmonization of Technical Requirements for Registration of Pharmaceuticals for Human Use. The Ethics Committee of the Medical Faculty of the University of Tübingen has approved the protocol, patient information, and consent form of this clinical trial (protocol version 1.1, approved on 03 July 2024, 614/2023BO1). All study participants will receive comprehensive information about the nature, scope, and procedures of the investigations and will give written informed consent prior to inclusion. Only patients who display sufficient capacity for insight, judgment, and consent (verified by qualified medical trial staff) will be included in the trial. In addition, all study participants will be informed of their right to discontinue participation in the study at any time without stating reasons and without disadvantages.

### Study centers and recruitment

Besides the Department of Psychiatry and Psychotherapy of the University Hospital Tübingen as the coordinating center, four additional German centers are planned to participate in the recruitment and treatment of study participants. Potential centers must meet the following requirements for participating: availability of the appropriate technical equipment and qualified personnel with experiences in the TMS treatment of depressive patients as well as the capacity to include at least 12 patients in the trial. The recruitment will take place in the outpatient departments of the participating centers. In addition, potential participants can be addressed by contacting local patient advocacy/support groups, local psychiatrists/general practitioners, as well as information via the respective clinic’s websites, social media, newsletters, local newspapers, and/or advertisement in public transportation.

### Patient involvement

The study was designed in cooperation with members of the German Center for Mental Health, (*Deutsches Zentrum für Psychische Gesundheit*, DZPG) stakeholder advisory board representing affected persons and relatives. Experts by Experience (EE) with lived experience regarding MDD are an integral part of our research team. They are regularly involved in the planning of the study, will support the trial until its completion and participate in the publication as well as dissemination of the results.

### Randomization

Randomization will take place after successful verification of the in- and exclusion criteria but before baseline measurements. The Institute of Clinical Epidemiology and Applied Biostatistics of the University of Tübingen (IKEaB) is responsible for randomization. By using the randomization tool of the software nQuery (release 8), a randomization list with varying block lengths was generated. According to this list the IKEaB created randomization envelopes with consecutive patient-ID. Each envelope contains the information whether a patient will start the treatment with either rTMS or the intake of escitalopram. Patients will be randomized by study staff not involved in the treatment.

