### Assessments

The screening consists of written informed consent, psychiatric examination including reviewing the inclusion- and exclusion criteria, documentation of sociodemographic data, physical and neurological examination, ATHF [34] and MADRS [35].

The baseline (R 0) comprises a pregnancy urine test (for women of childbearing age), determination of resting motor threshold (RMT), blood sampling, MADRS [35], Beck-Depression Inventory II (BDI-II) [36], patients’ preference regarding the treatment modality in Stage I, clinical global impression (severity scale) (CGI-S), World Health Organization Five Well-Being Index (WHO-5) [37], THINC-it Tool [38], Ruminative Response Scale-Short Form (RRS-short form) [39], General self-efficacy scale (GSE) [40], Rosenberg Self-Esteem Scale (RSES) [41], Credibility/ Expectancy Questionnaire (CEQ) [42], Childhood trauma questionnaire (CTQ) [43] and the Work Productivity and Activity Impairment Questionnaire (WPAI) [44].

During the treatment periods, the ratings R1-R4 will take place at the end of week two, four, six and eight. R2 (end of week 4) is the time point at which, among other ratings, the primary endpoint for this study is determined. R1 and R3 are interim evaluations only consisting of MADRS, BDI-II and CGI-I. R4 takes place at the end of Stage II. The follow-up rating R5 takes place after a three months period. The tests and questionnaires performed during Screening, Baseline, Ratings R1-R5 are summarized in Table 1.

With regard to the primary endpoint (MADRS) raters will be trained and blinded during the course of the study. The raters receive three videos explaining the ratings of the different MADRS items. A final video is used for evaluation, i.e. the question of whether the raters’ ratings correspond to the sample solution. Any discrepancies are discussed with the principal investigator and deviations of more than ± 1 point result in a repetition of the training. Based on these discussions, instructions for raters will be specified and communicated to all study centers.

**Table 1 Tab1:** Tests, questionnaires and adjunctive measures (pregnancy test in urine, blood sampling, ECG and resting motor threshold) performed during S (screening), BL (baseline), the treatment period (stage I and II) and the Fup (follow up) are summarized. *only in cases of rTMS treatment, **only in cases of SSRI treatment

	S	BL	Stage I				Stage II				Fup
Week	0	0	1	2	3	4	5	6	7	8	20
Day	-10- -1	0		12		26		40		54	137

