### Primary and secondary endpoints

The *primary endpoint* is the comparison of the two study arms with regard to therapy response (reduction of MARDS score ≥ 50%) after 4 weeks at the end of Stage I (R2).

*Secondary endpoints* are the comparison of the two study arms with regard to remission rates after 4 weeks at the end of Stage I (MARDS ≤ 10). Changes in the severity of depressive symptoms after Stage I and II in terms of differences in pre- and post-values of the MADRS and BDI-II as well as achievement of remission at the end of Stage II. The CGI-S/CGI-I to quantify the general clinical improvement. The WHO-5 to capture each patient’s assessment of change in his or her mental well-being [37]. Further secondary endpoints are changes in cognitive functioning measured by the THINC-it Tool [38], incidence of AEs/SAEs in the respective treatment stages and arms as well as dropout rates in the different treatment arms. Further instruments will provide information about mechanisms and potential predictive markers of treatment response: RRS-short form [39], CTQ, GSE [40], RSES [41], CEQ [42], and if applicable, the Shared decision-making questionnaire (SDM-Q) [45]. The WPAI is used to assess the impact of health conditions on work productivity and daily activities.

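### Randomisation precedes the baseline visit, so the reference MADRS for the primary endpoint and the Stage I preference may be collected from patients who already know their arm

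*Protocol article*

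**What the plan says.** All references are to the protocol article.

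- **Randomization:** "Randomization will take place after successful verification of the in- and exclusion criteria but before baseline measurements". The envelope contains the assigned treatment and is handled by staff who do not treat the patient.
- **Assessments and Table 1:** R0, on day 0, includes MADRS, BDI-II, CGI-S, WHO-5, THINC-it, several questionnaires and the patient's "preference regarding the treatment modality in Stage I". Table 1 lists randomisation in the same day-0 column. Its footnotes restrict the R0 motor threshold to one arm and the R0 blood sampling and ECG to the other: "only in cases of rTMS treatment, only in cases of SSRI treatment".
- **Patient allocation to Stage I and Stage II:** response is a "MADRS score reduction by ≥ 50% compared to baseline". The same response status steers the Stage II treatment.
- **Primary and secondary endpoints:** the primary endpoint is the "comparison of the two study arms with regard to therapy response" at R2, the end of week 4.
- **Design and methods:** the trial is a "two-stage therapy response-adapted, rater-blinded, randomized (1:1 ratio) and controlled study". The Discussion adds that there is no placebo control.
- **Screening:** a MADRS is also taken on days -10 to -1, before randomisation. No section names it as the reference for response.

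**The concern.** A baseline value is meant to be independent of allocation. Here the stated order puts allocation first, in a trial where the patient will recognise the arm as soon as it is disclosed. MADRS is scored by a trained, blinded rater but rests largely on what the patient reports. Relief or disappointment about the allocation could therefore enter the R0 score. Because response is a percentage reduction from that score, an arm-dependent shift at R0 can change who counts as a responder in the only confirmatory analysis. It would also enter the pre-post changes in MADRS and BDI-II listed as secondary endpoints.

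The preference item has a more direct problem. One stated aim is to bring in patients' treatment preferences, and the Background wants to examine how preferences influence success. A Stage I preference asked once the arm is known may be shaped by the assignment itself.

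**Working it through.** **1. The plan's own sample size.** Inputs from Sample size calculation: 40% and 60% response, margin 10 points, one-sided 0.025, power 80%.

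n per arm = (1.96 + 0.84)² × (0.4×0.6 + 0.6×0.4) / (0.20 + 0.10)² = 7.85 × 0.48 / 0.09 = 41.9, so 42 per arm and 84 in total. With 20% dropout, 42 / 0.8 = 52.5, so 53 per arm and 106 in total. The stated figures reproduce, and this point does not alter them.

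**2. The sequence.** Eligibility is checked, then the patient is randomised, then R0 takes place. R0 supplies the baseline MADRS and the preference. Some R0 procedures can only be done once the arm is known to staff, so the allocation is acted on during day 0. Nothing delays disclosure until after the ratings, but nothing gives the order within the day either.

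**3. How a baseline shift acts on response.** Let a shift d in R0 carry over to R2 by a fraction c. Response is then

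R2 + c·d ≤ 0.5 × (R0 + d), that is, R2 − 0.5·R0 ≤ (0.5 − c)·d.

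- c = 0: the threshold moves by +0.5d.
- c = 0.5: no effect at all.
- c = 1: the threshold moves by −0.5d, so the sign reverses.

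**4. Illustrative size.** The documents give no MADRS distribution, so these are assumptions: R0 about N(28, 5) truncated at 20, week-4 SD 7 to 9, R0/R2 correlation 0.3 to 0.5, 40% response without a shift.

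Hand check with the middle values (SD 8, correlation 0.4), ignoring truncation: SD of R2 − 0.5·R0 = √(64 + 6.25 − 16) = 7.37. The 40% point lies at z = −0.253.

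- d = +1, c = 0: Φ(−0.253 + 0.5/7.37) = 42.6%.
- d = +2, c = 0: Φ(−0.253 + 1/7.37) = 45.3%.
- d = +2, c = 1: Φ(−0.253 − 1/7.37) = 34.9%.

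Simulation over the full assumed range, with truncation:

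| Shift at R0 | Carry-over to week 4 | Response rate |
|---|---|---|
| +1 | none | 42.3–43.1% |
| +2 | none | 44.5–46.4% |
| +2 | half | 40.0% |
| +2 | full | 33.9–35.6% |

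A second model (R0 mean 26 to 30, SD of fractional change 0.25 to 0.35, starting from 40% or 60% response) gives about 2 to 3 points for a 1-point shift and about 4 to 6 points for a 2-point shift, again without carry-over.

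**5. Effect on the confirmatory test, if such a bias existed.** With 42 per arm and a true difference of −10 points (30% v 40%), SE = √(0.21/42 + 0.24/42) = 0.1035. The false non-inferiority rate is 1 − Φ(1.96 − bias/0.1035) when the bias favours rTMS. When it favours SSRI, power at the planning rates is Φ((0.30 − bias)/0.1069 − 1.96), with 0.1069 = √(0.48/42).

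| Bias (points) | False non-inferiority, bias favours rTMS | Power, bias favours SSRI |
|---|---|---|
| 0 | 0.025 | 80% |
| 2 | 0.039 | 75% |
| 3 | 0.047 | 71% |
| 4 | 0.058 | 68% |
| 6 | 0.084 | 61% |

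**The case against.** The strongest reply has four parts.

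- **Disclosure is not documented.** Randomisation and R0 share day 0, and the envelope is handled by staff outside the treatment team. A site could complete the MADRS before telling the patient. This stands as a limit on certainty. It does not clear the plan, because the written order permits the opposite and nothing prevents it.
- **The bias has no known sign or size.** The patient is as unmasked at week 4 as at R0, half carry-over cancels the effect, and full carry-over reverses it. Relief and disappointment may also partly cancel within an arm if preferences are mixed. This stands in full: the figures above show what is possible, not what is expected.
- **A clean value exists.** The screening MADRS precedes randomisation and allows a check. This is true and lowers the stakes, but the plan does not use it as the reference for response.
- **Expectation belongs to the chosen comparison.** The Discussion accepts expectation effects as part of real-world use. That defends unmasked treatment. It does not defend an unmasked baseline, which should be free of any treatment influence.

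A reader might also infer that R0 values are spoiled as covariates, or that the whole preference aim fails. The documents do not support either. The Statistical analysis section names only unadjusted methods, with no model using R0. The Stage II shared decision takes place after R2 and is not touched by this order; only the Stage I preference item is exposed.

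**Conclusion.** The point holds as a fault in sequence. The article fixes randomisation ahead of the measurements that supply the reference value for its only confirmatory endpoint, in a trial where patients cannot be masked. This is a stated rule, not detail left to a fuller document.

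That patients know their arm at the R0 MADRS is an inference. It rests on the envelope naming the arm, the unmaskable treatments and the arm-specific R0 procedures. A reader might go further and conclude that the primary result will be biased in a given direction by about half the margin. The documents do not support that: the 2 to 6 point range assumes a net 1 to 2 point shift in one arm, no carry-over to week 4, and a MADRS distribution that the article does not give.

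For the Stage I preference no arithmetic is needed. Recorded after allocation, it cannot be relied on as a pre-treatment preference.

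**What to change.** Reorder R0 within the same visit:

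1. Complete MADRS, BDI-II, CGI-S, WHO-5, THINC-it, the other questionnaires and the Stage I preference.
2. Open the envelope.
3. Carry out the arm-specific procedures.

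Amend the Randomization section and Table 1 to match. If the CEQ is meant to rate the assigned treatment, it belongs after step 2, and the protocol should say so. If sites already withhold the allocation until the ratings are done, correcting the text is enough.

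For patients already enrolled under the present order, add a sensitivity analysis of the primary endpoint with the pre-randomisation screening MADRS as reference. A second check of the MADRS entry threshold at R0 is not needed: it would add an eligibility gate that the bias argument does not call for.

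The cost is revised wording, a site instruction and a small change in workflow. There are no extra visits or assessments, and the sample size stays at 84 evaluable and 106 recruited.
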